| 1. Prohibited Concomitant Medications and Therapies   1) In principle, subjects will be prohibited from taking any of the following medications unless the principal investigator or subinvestigator allows the concomitant use in response to acute exacerbation:  ATP solution (e.g., Adetphos^Ⓡ^), Vitamin B12 solution (e.g., Methycobal^Ⓡ^), Betahistine (e.g., Merislon), and medications that improve microcirculation (e.g., Kallikrein).  2) Subjects will be prohibited from concomitant use of medications described below.  Sirolimus is metabolized by a drug-metabolizing enzyme, CYP3A4, and is a substrate for P-glycoprotein. Sirolimus itself is an inhibitor of CYP3A4. Subjects are thus prohibited from taking any of the systemic medications and foods listed below throughout their participation in this clinical trial, i.e., from the initial administration of investigational products (V1) to the end of the administration (V12).   \| Influencing factors \| Medications and foods \| Rationale \| \| --- \| --- \| --- \| \| 1) Inhibition of mTOR \| everolimus; temsirolimus \| The products have the same mechanism of action as the investigational products, which would disturb efficacy analysis. \| \| 2) Influence on the assessment of the disease studied \| aminoglycoside class of antibiotics; platinum-based drugs \| Ototoxicity of the products could exacerbate inner ear disorder. (Topical administration is allowed.) \| \| 3) Live vaccines \| live vaccines (e.g., measles, mumps, rubella, oral polio, BCG) \| The immunosuppresive properties of sirolimus may cause proliferation of microorganisms in live vaccines leading to enhanced virulence.  (The package insert of Rapamune states these as contraindications for concomitant use.) \| \| 4) Induction of CYP3A4 \| anticonvulsants (e.g., carbamazepine, phenobarbital, phenytoin); rifampicin*; rifabutin; foods containing St. John’s Wort (*Hypericum perforatum*) \| The products induce CYP3A4 and may lower blood concentrations of the investigational products.  (*Rifampicin induces P-glycoprotein and thus may stimulate removal of the investigational products from cells.) \| \| 5) Inhibition of CYP3A4 \| ciclosporin**; diltiazem**, triazole antifungal (e.g., fluconazole, ketoconazole**, itraconazole, voriconazole); HIV protease inhibitors (e.g., indinavir, ritonavir, telaprevir, saquinavir); macrolide class of antibiotics (e.g., erythromycin, clarithromycin); calcium channel blocker (e.g., nicardipine, verapamil); cimetidine; metoclopramide; bromocriptine; danazol; grapefruit juice \| The products significantly inhibit CYP3A4, and may raise blood concentrations of the investigational products. (Topical administration is allowed.)  (**These products inhibit P-glycoprotein and thus may hinder removal of the investigational products from cells.) \| \| 6) Inhibition of CYP3A4 by ritonavir \| ombitasvir hydrate; paritaprevir hydrate; ritonavir \| Inhibition of CYP3A4 by ritonavir may raise AUC and C_max_ of the investigational products. \| \| 7) Mechanism unidentified \| micafungin sodium \| The product may increase AUC of the investigational products. \| \| 8) Other effects \| angiotensin-converting-enzyme inhibitor \| For a patient taking medications related to angioedema, the product may increase risks of onset of angioedema (e.g., swelling of face, lips, tongue, or throat). (Mechanism unidentified) \| |

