Estimated glomerular filtration rate (eGFR) lower than 30 mL/min/1.73 m^2^

7) Immunodeficiency such as HIV or primary immunodeficiency

8) Inability to take investigational products in tablet form, or gastrointestinal dysfunction with risks of malabsorption of sirolimus

9) History of having surgery within eight weeks prior to the registration (any surgery that requires invasion of the body or suture with three or more stitches, including biopsy)

10) Female patients who are pregnant, potentially pregnant, or breastfeeding. Male or female patients who decline to consent to contraception during the trial

Contraceptive methods: Combination of condoms and spermicide; combination of condoms and diaphragms with spermicide; oral contraceptive; intrauterine contraceptive device; or other methods

11) Need to take medications that influence CYP3A4 activation after the administration of investigational products

12) Pulmonary interstitial opacity

13) Diagnosis by the attending physician during the screening phase or from previous observations from hearing tests that the hearing loss is fixed rather than fluctuating

14) Participation in other clinical research and/or trials within six months prior to the date of consent, with the exception of Analysis of Diseases in Otorhinolaryngology Using iPS Cells (approval No. 20140172)

15) Other conditions that the principal investigator or subinvestigator deems inappropriate

[Rationale]

1) through 7), 9) through 12), and 15) To ensure patients’ safety and to assess safety appropriately

8) The situation disturbs prediction of pharmacokinetics of the investigational products.

13) and 14) These may influence analysis of the investigational products.

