# Prohibited Concomitant Medications and Therapies

1) In principle, subjects will be prohibited from taking any of the following medications unless the principal investigator or subinvestigator allows the concomitant use in response to acute exacerbation:

ATP solution (e.g., Adetphos^Ⓡ^), Vitamin B12 solution (e.g., Methycobal^Ⓡ^), Betahistine (e.g., Merislon), and medications that improve microcirculation (e.g., Kallikrein).

2) Subjects will be prohibited from concomitant use of medications described below.

Sirolimus is metabolized by a drug-metabolizing enzyme CYP3A4, and is a substrate for P-glycoprotein. Sirolimus itself is an inhibitor of CYP3A4. Subjects are thus prohibited from taking any of the medications and foods listed below throughout their participation in this clinical trial, i.e., from the initial administration of investigational products (V1) to the end of the administration (V12).

| Influencing factors | Medications and food | Rationale |
| --- | --- | --- |
| 1) Inhibition of mTOR | everolimus; temsirolimus | The products have the same mechanism of action as the investigational products, which would disturb efficacy analysis. |
| 2) Influence on the assessment of the disease studied | aminoglycoside class of antibiotics; platinum-based drugs | Ototoxicity of the products could exacerbate inner ear disorder.  (Topical administration is allowed.) |
| 3) Live vaccines | live vaccines (e.g., measles, mumps, rubella, oral polio, BCG) | The immunosuppresive properties of sirolimus may cause proliferation of microorganisms in live vaccines leading to enhanced virulence.  (The package insert of Rapamune states these as contraindications for concomitant use.) |
| 4) Induction of CYP3A4 | anticonvulsants (e.g., carbamazepine, phenobarbital, phenytoin); rifampicin*; rifabutin; foods containing St. John’s Wort (*Hypericum perforatum*) | The products induce CYP3A4 and may lower blood concentrations of the investigational products.  (*Rifampicin induces P-glycoprotein and thus may stimulate removal of the investigational products from cells.) |

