| 5) Inhibition of CYP3A4 | ciclosporin**; diltiazem**, triazole antifungal (e.g., fluconazole, ketoconazole**, itraconazole, voriconazole); HIV protease inhibitors (e.g., indinavir, ritonavir, telaprevir, saquinavir); macrolide class of antibiotics (e.g., erythromycin, clarithromycin); calcium channel blocker (e.g., nicardipine, verapamil); cimetidine; metoclopramide; bromocriptine; danazol; grapefruit juice | The products significantly inhibit CYP3A4, and may raise blood concentrations of the investigational products.  (Topical administration is allowed.)  (**These products inhibit P-glycoprotein and thus may hinder removal of the investigational products from cells.) |
| 6) Inhibition of CYP3A4 by ritonavir | ombitasvir hydrate; paritaprevir hydrate; ritonavir | Inhibition of CYP3A4 by ritonavir may raise AUC and C_max_ of the investigational products. |
| 7) Mechanism unidentified | micafungin sodium | The product may increase AUC of the investigational products. |
| 8) Other effects | angiotensin-converting-enzyme inhibitor | For a patient taking medications related to angioedema, the product may increase risks of onset of angioedema (e.g., swelling of face, lips, tongue, or throat). (Mechanism unidentified) |

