## Subjects’ Baseline Information

The principal investigator or subinvestigator will collect the baseline information listed below from each subject during the period between informed consent and before administration of the investigational products in V1 (D1), and record the information on the subject’s electronic case report form. For the purpose of this protocol, an illness that has not subsided before administration of the investigational products is referred to as a concomitant illness, and one that has subsided as a past medical history. The results of SLC26A4 genetic testing will not be recorded on the electronic case report form.

・Date of birth

・Gender

・Height and weight

・History of head trauma

・Concomitant illness

・Prior treatment (cisplatin and gentamicin)

・Concomitant medications

・SLC26A4 Genetic testing results

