## Discontinuation Criteria

### Participant Withdrawal

The principal investigator or subinvestigator will withdraw a subject from the trial if he/she meets any of the criteria listed below. On withdrawal of the clinical trial, the principal investigator or subinvestigator will immediately secure the safety of the subject and take appropriate measures. When a subject is withdrawn from the clinical trial, reasons for the withdrawal and occurrence of adverse events will be identified and recorded in the source document and on the electronic case report form. Tests that are scheduled at discontinuation will be performed as far as practical.

1) Subject’s request for withdrawal from the trial

2) Subject no longer trackable

3) Discovery of obvious ineligibility for participation in the trial

4) Decision of the principal investigator or subinvestigator that the subject’s participation in the trial would be difficult due to an adverse event that occurs after the initiation of the trial

5) Pregnancy of the subject

6) Death of the subject

7) Need for dosage reduction below the lowest standard of one 1-mg tablet every three days, administered orally

8) Other conditions that the principal investigator or subinvestigator deems appropriate for withdrawal

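### The ban on ototoxic drugs allows topical use at any site, so aminoglycoside ear drops are permitted from V1 to V12 and are not a deviation

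*Protocol*

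**What the plan says.** The list of prohibited medications appears twice, in the Protocol Summary and in the body section Prohibited Concomitant Medications and Therapies. In both, row 2 is headed as concerning influence on the assessment of the disease, and it names aminoglycoside antibiotics and platinum-based drugs. The synopsis gives the reason and the exception together: "Ototoxicity of the products could exacerbate inner ear disorder. (Topical administration is allowed". The body gives the same reason, "Ototoxicity of the products could exacerbate inner ear disorder", with the same exception for topical use. Neither table defines *topical* or excludes a site.

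The lead sentences differ. In the synopsis subjects are "prohibited from taking any of the systemic medications and foods listed below". In the body they are "prohibited from taking any of the medications and foods listed below throughout their participation in this clinical trial", without the word *systemic*. Both set the period as V1 to V12.

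Row 5 carries the same topical exception, but for a different reason: "The products significantly inhibit CYP3A4, and may raise blood concentrations of the investigational products".

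**The concern.** Row 2 keeps ototoxic drugs away from subjects whose hearing is being measured. A topical exception with no site limit leaves open the one site where local application is closest to the organ at risk. An outside doctor could prescribe aminoglycoside ear drops and the subject would remain fully within the rule.

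Two things are at stake. The first is exposure that could be avoided in people with an inner ear disorder. The second is interpretability. Under Efficacy Endpoints, an audiometric change of 10 dB or more counts as a hearing loss episode, and ears and frequencies are counted separately. With four frequencies tested per ear, a shift across one ear could give up to 1 × 4 = 4 counted episodes. That is conditional on a shift occurring, and the protocol offers no evidence that ear drops would cause one. The planned arms are small (12 active, 4 placebo), so a single affected subject would not be diluted much.

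**Working it through.** The plan gives no figure on this point and no arithmetic settles it. The check is a reading of every provision that could permit or forbid the use.

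1. **Drug class.** Aminoglycosides are named in row 2 of both tables, so they fall under the ban unless the exception applies.
2. **Route.** The exception covers topical administration and excludes no site. In ordinary usage ear drops are topical, so the exception applies.
3. **Lead sentence.** The synopsis restricts the whole list to systemic medications, which independently leaves ear drops outside the ban. The body sentence lacks that restriction, but its row 2 exception gives the same result. Both versions of the rule permit the drops.
4. **Other provisions that might close the gap.**
   - Exclusion criterion 15 under Study Population ("Other conditions that the principal investigator or subinvestigator deems inappropriate") and withdrawal criterion 8 under Participant Withdrawal ("Other conditions that the principal investigator or subinvestigator deems appropriate for withdrawal") give general discretion. Neither forbids a particular drug or route.
   - Oversight of Subjects asks subjects to report medicines obtained elsewhere. Concomitant Medications and Therapies has them recorded from V0 to V13, and the daily questionnaire also collects them. These provisions record use; they do not restrict it.
   - Subjects' Baseline Information collects "Prior treatment (cisplatin and gentamicin". This is history before dosing and says nothing about routes allowed during the trial.
5. **Deviation status.** Protocol Deviations or Changes requires all deviations to be recorded. A permitted medication is not a deviation, so ear-drop use would not be recorded as one.
6. **Comparison with row 5.** There the worry is the blood concentration of the investigational product, and a topical exception with no site limit fits that worry. In row 2 the worry is the inner ear, and the same wording fits less well, because site matters to the reason given.

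Result: no provision prohibits aminoglycoside ear drops between V1 and V12.

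**The case against.** The strongest reply is that the protocol never mentions ear drops, and that nothing in it shows that an aminoglycoside placed in the ear reaches the inner ear. Row 2 names no route in its reason and can be read as a ban on systemic exposure, as the synopsis lead sentence says outright. Repeating the exception in both tables suggests a deliberate choice. Use would also be visible: medications are reported and recorded, and the purpose of each is entered on the case report form. The analysis-set standards, due before database lock, could use those records without a deviation label.

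Much of this stands. No effect on hearing can be claimed, and an intent to allow skin or eye use is reasonable. The exception does not strictly contradict the row; it sits badly with the row's reason when the site is the ear. What the reply does not remove is the permission itself. Recording neither prevents exposure nor makes it a deviation.

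A reader might infer more than the documents support:
- **That the hearing endpoints are biased.** There is no rate of use and no effect size in the protocol.
- **That the length of the ban measures the problem.** The ban runs 36 weeks, out of 42 scheduled weeks of home audiometry from week -2 to week 40. This is only a window, and it would be the same for any row of the table.
- **That platinum-based drugs are equally affected.** They share the row, but the practical point concerns aminoglycosides.
- **That intratympanic treatment is permitted.** The protocol does not say whether it counts as topical.
- **That *systemic* in the synopsis is an error to delete.** The documents do not show which lead sentence was intended.

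**Conclusion.** The point holds in a limited form. As written, aminoglycoside ear drops comply with the medication rule from V1 to V12, in a row whose purpose is to protect the inner ear. This rests on one assumption, that *topical* has its ordinary meaning and includes ear drops, since the protocol does not define it. The size of any effect on the hearing endpoints is unknown and may be zero. Efficacy is a secondary objective in this exploratory trial, and concomitant use would be on record in any case. It is a cheap improvement of low severity, and it does not call any planned analysis into question.

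**What to change.** In row 2 of both tables, replace the exception with: *(Topical administration is allowed, except application to the ear, including ear drops and intratympanic use, which is prohibited.)* Naming intratympanic use settles its status.

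In the synopsis lead sentence keep *systemic* and add *unless a row states otherwise*. Without this addition the lead sentence would still exempt ear drops whatever the cell says. Deleting *systemic* instead would widen the synopsis ban for the six of eight rows that have no topical exception of their own (8 − 2 = 6), which this point does not require.

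Application to the ear between V1 and V12 then becomes a recorded deviation, and the analysis-set standards can say how to handle it. The change does not alter the episode definition or remove such subjects from the FAS, and it does not reach the screening and follow-up weeks outside the ban.

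The cost is one clause in two table cells and one phrase in a lead sentence, with no new data collection. The downside is that a subject who needs ear treatment must use a drug outside the banned classes or be recorded as a deviation.

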# Background and Rationale

## Pendred syndrome/DFNB4

Pendred syndrome/DFNB 4 (PDS) is a disorder first described by Vaughan Pendred in 1896, the main symptoms of which include fluctuating and progressive hearing loss, persistent vertigo, and goiter (Pendred V, Lancet 1896; ii; 532). PDS is a rare genetic disorder caused by autosomal recessive disorder, and with an estimated 4,000 patients in Japan, it affects the second largest patient population among hereditary hearing disorders in the country. While the *SLC26A4* gene, which encodes pendrin, an anion exchanger, is known to be responsible for PDS (Everett LA, Nature Genetics. 1997; 17(4):411-22), the mechanism that leads to fluctuation and progressive cochlear disorder had long remained unknown. PDS patients with fluctuating hearing loss experience volatile changes in hearing acuity, and thus they suffer not only inconveniences in their daily life, but also fear of losing their ability to communicate orally with people around them following every acute exacerbation. Symptoms of PDS involve rotating vertigo that may last a few hours to a few days once it occurs, in addition to chronic dizziness, which are grave detriments to the patients’ quality of life.

No medication for hereditary hearing loss has pathophysiologically confirmed non-clinical POC anywhere in the world. For PDS, there is no effective treatment available at this time. The only effective interventions that exist are use of devices to augment hearing, such as hearing aids and cochlear implants. Although appropriate adjustment of a hearing aid requires consultation at a medical institution or with an audiologist, volatility in hearing and sporadic occurrence of fluctuations in a PDS patient impede the full performance of such adjustment. The hearing loss in PDS can progress as it fluctuates, and a PDS patient whose symptoms have progressed to severe hearing loss has an option to have a cochlear implant. Although the device provides a sense of sound, the sound quality is significantly deteriorated compared to what can be perceived with inner hair cells, as the number of electrodes used in a cochlear implant is limited to around twenty to date. With regard to vertigo, no medical intervention exists today, and thus patients have no option but to have bed rest and wait until the episode abates.

## Challenges in PDS Research and Background of Development of This Therapy (iPS Drug Discovery)

As described above, PDS is a rare and intractable disorder with no causal treatment, causing significant loss of patients’ QOL, and thus a new treatment has long been awaited. PDS is a hereditary disorder, and a knockout mouse for the *Slc26a4*, the responsible gene, develops severe hearing loss from severe malformation. A knock-in mouse for H723R mutations, the most commonly reported mutations in Japanese population with hearing impairment, however, does not develop deafness. This means that fluctuating and progressive hearing loss is not recapitulated in these mouse models. The lack of animal models is one of the impediments to understanding the pathology and developing treatments, and a reason that PDS treatments continue to depend on hearing devices.

We have described that this discrepancy is attributable to the species difference between primates and rodents, i.e., in primates, a family protein with similar functions and SLC26A4 co-express (Hosoya M et al, Neurosci. Res., 2016 Sep;110:1-10). This suggests that animal models generally used to demonstrate non-clinical POC in drug discovery research are essentially inapplicable to PDS due to species difference. Considering this fact, we have undertaken preclinical studies for iPSC-based drug discovery as part of research by [name], a co-investigator, et al. at Keio Center for the Program for Intractable Diseases Research Utilizing Disease-specific iPS cells of AMED (Japanese Unexamined Patent Application Publication 2015-231365); identified pathophysiology of a neurodegenerative disorder that involves protein aggregation as a new pathophysiological mechanism of cochlear hearing loss; and performed drug screening with cell death suppression as metrics (Hosoya M et al., Cell Reports, 2017, 3;18(1):68-81). We have discovered in this research that patient-derived iPS cells of inner ear present intracellular aggregations of mutant protein and vulnerability to cellular stress, which shares similarities in physiopathology with Parkinson’s disease and Alzheimer’s disease. We further screened existing drugs based on this finding, and identified sirolimus, an mTOR inhibitor, as an inhibitor of cell death. The minimum effective concentration required for inhibition of cell death was 0.9 ng/mL, which was less than 1/10 of the approved dose of sirolimus preparation (PCT/JP2016/05086, WO2016/117431).

The natural history of inner ear disorder in PDS patients presents recurrent transient episodes and indolent progression. As no correlation is observed between inner ear malformation and hearing loss in PDS, hypofunction rather than malformation of the inner ear is assumed to be a therapeutic target for the disorder.

We constructed three different in vitro cell models that correspond to PDS pathophysiology, using the disease-specific cells generated from patient-derived iPS cells: (1) acute injury from exposure to high-concentration epoxomicin; (2) acute injury from exposure to low-concentration epoxomicin; and (3) chronic injury without exposure to any agents. Sirolimus 0.9 ng/mL significantly reduced cell death in all three models.

The results suggested low-dose sirolimus for PDS patients suffering from exacerbating and progressive symptoms aggravated by life stressors and head trauma may ameliorate vulnerability of the patient’s inner ear cells, and further suggested this may lead to attenuation of hearing loss and vertigo episodes and decelerated progression due to reduced cell death.

